# Glucocorticoid Receptor (GR) antagonism as disease-modifying treatment for MDD with childhood trauma: protocol of the RESET-medication randomized controlled trial

**DOI:** 10.1186/s12888-023-04830-9

**Published:** 2023-05-11

**Keywords:** Major depressive disorder, Childhood trauma, Glucocorticoid receptor, Mifepristone, Randomized controlled trial

## Abstract

**Background:**

Major depressive disorder (MDD) is a heterogeneous psychiatric disorder. Childhood trauma (CT, emotional/physical/sexual abuse or neglect before the age of 18) is one of the largest and most consistent risk factors for development and poor course of MDD. Overactivity of the HPA-axis and the stress hormone cortisol is thought to play a role in the vulnerability for MDD following exposure to CT. Rodent experiments showed that antagonism of the glucocorticoid receptor (GR) at adult age reversed the effects of early life stress. Similarly, we aim to target MDD in individuals with CT exposure using the GR antagonist mifepristone.

**Methods:**

The RESET-medication study is a placebo-controlled double-blind randomized controlled trial (RCT) which aims to include 158 adults with MDD and CT. Participants will be randomized (1:1) to a 7-day treatment arm of mifepristone (1200 mg/day) or a control arm (placebo). Participants are allowed to receive usual care for MDD including antidepressants. Measurements include three face-to-face meetings at baseline (T0), day 8 (T1), week 6 (T2), and two online follow-up meetings at 12 weeks (T3) and 6 months (T4). A subgroup of participants (*N* = 80) are included in a fMRI sub-study (T0, T2). The main study outcome will be depressive symptom severity as measured with the Inventory of Depressive Symptomatology—Self Rated (IDS-SR) at T2. Secondary outcomes include, among others, depressive symptom severity at other time points, disability, anxiety, sleep and subjective stress. To address underlying mechanisms mifepristone plasma levels, cortisol, inflammation, epigenetic regulation and fMRI measurements are obtained.

**Discussion:**

The RESET-medication study will provide clinical evidence whether GR antagonism is a disease-modifying treatment for MDD in individuals exposed to CT. If effective, this hypothesis-driven approach may extend to other psychiatric disorders where CT plays an important role.

**Trial registration:**

The trial protocol has been registered 01–02-2022 on ClinicalTrials.gov with ID “NCT05217758”.

**Supplementary Information:**

The online version contains supplementary material available at 10.1186/s12888-023-04830-9.

## Background

Major depressive disorder (MDD) is a recurrent and progressive psychiatric disorder [1, 2], and a leading cause of disability [3]. Around 10–30% of patients do not benefit from evidence-based treatments such as antidepressants and psychotherapy [4]. It is increasingly clear that MDD is a heterogeneous disorder with varying clinical phenotypes [5, 6]. Accordingly, novel therapeutic strategies for MDD may target specific subtypes of MDD, such as immunometabolic depression [7]. Childhood trauma (CT, emotional/physical/sexual abuse or neglect before the age of 18) is one of the most consistent risk factors for both developing MDD and a poorer course of disease [8, 9]. Estimates of CT prevalence in MDD vary, but it is thought that between 25 to 75% of MDD patients have experienced moderate to severe CT [10]. MDD following exposure to CT typically emerges earlier in life with more severe and chronic symptoms [11–13], more anxiety, suicidality, and insomnia, and reduced daily functioning [14, 15]. There is an unmet need for treatments that target the high burden of MDD with CT exposure.

CT is thought to activate the hypothalamic–pituitary–adrenal (HPA) axis and elevate cortisol in a sensitive developmental period. The effects of cortisol are likely mediated by binding to glucocorticoid receptors (GR) that are widely distributed in the brain. These processes early in life may result in long-lasting maladaptive effects on stress vulnerability and result in overall poorer (mental) health including an increased MDD risk [16]. There is compelling evidence for the changes in brain function and behaviour that may underlie disease vulnerability. These include structural and functional changes in brain networks [17, 18], working memory [19–21], emotional regulation [22–24], HPA-axis functionality [16, 25], and increased inflammation [26], but also psychological and lifestyle mechanisms [27].

In line with the notion of an overactivated HPA-axis during, and possibly after stress in early life, treatment with a GR antagonist emerges as a promising strategy from the animal literature [28–31]. In several studies, administration of the GR-antagonist mifepristone in adolescent rodents exposed to early life stress reversed increased freezing behaviour at adult age [28] and normalized open-field behaviour and corticosterone levels when administered at adult age [31]. Mifepristone also reversed changes in social behaviour in animals stressed during adolescence [30]. Thus, in rodents, the GR antagonist mifepristone seems to be able to counteract long-term GR overactivation following early life stress. In humans, such effects of GR antagonism have not been examined. Nevertheless, the GR antagonist mifepristone has been widely used for decades to treat Cushing’s syndrome [32]. Based on beneficial effects on psychiatric symptoms observed in Cushing’s disease, mifepristone has also been investigated for psychotic depression (7-day mifepristone regimen 300–1200 mg/day) [33–38]. A combined analysis of five RCTs showed an overall significant effect of mifepristone (*N* = 793) vs. placebo (*N* = 595) in reducing psychotic symptoms in psychotic depression, but significantly more so in patients with high plasma mifepristone levels after 7 days (d = 0.3) compared to low plasma levels (d = 0.05) [39]. From these studies, a 7-day mifepristone treatment is known to be generally well-tolerated and adverse events (AEs) were not significantly different compared to placebo treatment.

The REStoring mood after Early life Trauma (RESET) study is a double-blind, placebo-controlled, randomized trial that tests the hypothesis whether a 7-day treatment using the GR antagonist mifepristone (1200 mg) improves depression in patients with moderate to severe MDD and CT.

## Methods

### Study design

This is a mono-center, placebo-controlled, double-blind randomized controlled trial (RCT) testing the efficacy of a 7-day treatment of mifepristone (1200 mg/day) or placebo in *N* = 158 patients with MDD and CT. The study consists of 5 measurement time-points: baseline (T0), post-intervention at 1 week (T1), 6 weeks (T2) after the start of the intervention, and two online follow-up measurements (T3 at 12 weeks, T4 at 6 months) (see Fig. 1). The optional (f)MRI sub-study is conducted at separate visits around the T0 and T2 time points. Throughout the study, participants are allowed to continue or start their treatment as usual (TAU) in parallel to the RCT. The RESET-medication protocol is reported according the SPIRIT guidelines and methodology [40] (see Additional file 1).

**Fig. 1 Fig1:**
[figure not shown]
Flowchart of the RESET-medication time-points and measurements. Created with BioRender.com

### Recruitment and study settings

Recruitment of participants occurs through a study website (www.jeugdtrauma-depressie.nl), where information can be found about the RCT and how to participate. The study website is advertised on websites of the Dutch patient federation for depression ‘Depressievereniging.nl’, the subsidy party ‘Hersenstichting.nl’, and (social) media. Also, at several mental health clinics throughout the Netherlands therapists treating patients with MDD and CT inform patients about the RESET study.

The study website screens for suitable participants based on depressive symptoms (Inventory of Depression Severity – Self Rated; IDS-SR) and CT (short form of the Childhood Trauma Questionnaire; CTQ-SF). Eligible participants are contacted by research assistants (RAs) within 2 weeks via telephone for further screening. If the participant is deemed suitable for participation, the information letter is sent out to consider all relevant information regarding participation. Once participants agree to participate, T0, T1, T2 visits are conducted at the research center of Amsterdam UMC, location VUmc. Follow-up measurements at T3, T4 are conducted via video calling and online questionnaires. The optional fMRI sub-study is conducted at the Spinoza center for neuroimaging in Amsterdam, the Netherlands. All measurements are performed by certified RAs. Participants receive €20 for each RCT study time-point (T0-T5), and €30 for each fMRI visit (T1, T2).

### Eligibility criteria

Inclusion criteria are: 1) Age of ≥ 18 years and able to give written informed consent (IC); 2) current moderate to severe depression with a score of ≥ 26 on the IDS-SR; 3) DSM-5 diagnosis of MDD confirmed with clinical interview (Mini International Neuropsychiatric Interview—Simplified; MINI-S) during T0; 4) Moderate to severe CT before the age of 18 with a score above a validated cut-off for moderate to severe CT on one or more of the following domains using the CTQ-SF: physical neglect: score ≥ 10, emotional neglect: score ≥ 15, sexual abuse: score ≥ 8, physical abuse: score ≥ 10; emotional abuse: score ≥ 13; 5) Women of child bearing potential (WOCBP) agree to use a non-hormonal contraceptive method (e.g. condom) during the intervention period and up to 1 month after the intervention based on the abortive effects of mifepristone via progesterone receptor antagonism.

Exclusion criteria are primarily checked by self-report during the telephone screening and consist of: 1) primary diagnosis of post-traumatic stress disorder (PTSD) or Acute Stress Disorder (ASD) where a diagnosis must have been received from a physician/mental health practitioner; 2) Lifetime diagnosis of borderline personality disorder (BPD), bipolar disorder, schizophrenia or current substance abuse where a diagnosis must have been received from a physician/mental health practitioner; 3) Start of depression treatment (e.g. psychotherapy, antidepressants) in the week before or after the start of the intervention. Hereby, study participation does not intervene with patient needs of treatment; 4) Chronic adrenal insufficiency, diagnosed by a physician; 5) Female participants that have a history of unexplained vaginal bleeding or endometrial changes. 6) Female participants that are pregnant or breastfeeding. Pregnancy is excluded using a negative pregnancy test during the baseline visit; 7) Current use of drugs being CYP3A4 inhibitors/inductors/substrates, CYP2C8/9 substrates, glucocorticoid antagonists and systemic corticosteroids. A list of exclusion drugs is used for screening to prevent interactions with mifepristone. See Table 1 for an overview of the in- and exclusion criteria.

**Table 1 Tab1:** Overview of inclusion and exclusion criteria

**Inclusion criteria**	**Exclusion criteria**
1. Age of ≥ 18 years	1. Primary PTSD or ASD
2. Moderate/severe MDD	2. Lifetime BPD, bipolar disorder, schizophrenia or current substance abuse
3. Moderate/severe CT	3. Start of depression treatment in the week before or after the start of the intervention
4. For WOCBP, use of a non-hormonal contraceptive method (e.g. condom) during the intervention period and up to 1 month after the intervention	4. Chronic adrenal insufficiency
	5. A history of unexplained vaginal bleeding or endometrial changes.
	6. Pregnancy or breastfeeding
	7. Current drug use of CYP3A4 inhibitors/inductors/substrates, CYP2C8/9 substrates, glucocorticoid antagonists and systemic corticosteroids

### Sample size

Based on preclinical evidence [28–31] and our targeted treatment of MDD with moderate to severe CT in RESET, we hypothesize a larger effect size compared to clinical trials of psychotic depression with an effect size of d = 0.3 [39]. Therefore, it is estimated that this targeted disease-modifying treatment in a clinically specific group may have a robust treatment effect on the primary outcome measure with a medium effect size (Cohen’s d = 0.50, α = 0.05, two-tailed, power 80%). This requires 63 participants per group. Previous randomized studies in psychotic depression using a 7-day mifepristone treatment (300–1200 mg/day, *N* = 1388) found average dropout rates of around 20% [39]. Therefore, a total sample size of *N* = 158 is required, with *N* = 79 in each treatment arm of mifepristone and placebo.

For the (f)MRI sub-study, 40 participants will be included per treatment arm (total of *N* = 80). This required sample size is calculated for our primary fMRI outcome measure: dynamical resting-state connectivity in response to a Trier Social Stress Test (TSST) [41]. Here we specifically aim to detect the influence of mifepristone vs. placebo on variation in network connectivity between the acute and recovery phase of this stress response. Currently, the effect size of mifepristone on these dynamics is unknown. However, we do know that the difference in resting-state network connectivity between the acute and delayed response phase is medium in healthy individuals (Cohen's f = 0.315) [42]. We also know from work in rodents that mifepristone has a medium effect on the structural integrity of the brain (Cohen's f = 0.316) [43]. Therefore, we want to be able to detect a medium effect size in our fMRI sub study. Calculations using R-package WebPower [44] revealed that we need two equal groups of 40 individuals to detect a medium effect (Cohen's f = 0.32) in within-between subject interactions in a repeated-measures ANOVA with 2 groups (i.e. placebo and mifepristone) and 2 measures (i.e. acute and delayed phase), and obtain a power of 80 percent with type I error rate of 0.05.

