### Neuro-imaging

In order to test for potential neurobiological effects of mifepristone treatment, a (f)MRI sub-study will be conducted in a sub-group of *N* = 80 patients (*N* = 40 per group), at baseline (T0) and repeated at post-intervention (T2). Within each visit (T0, T2) there are two (f)MRI sessions which will be conducted after the TSST in order to assess the acute (0–40 min) and recovery (60–100 min) phases of stress system dynamics in response to a psychosocial stressor. The scanning procedure consists of anatomical scans (T1, Diffusion Tensor Imaging; DTI), functional resting-state, and two commonly used fMRI tasks: 1) N-back working memory task [65] where participants are presented a series of stimuli one-by-one and are asked to decide for each stimulus whether it matches the one displayed n (1,2, 3, etc.) trials ago. 2) Situation-focused volitional reappraisal task [66] where participants are presented with positive, negative or neutral pictures and are asked to either positively reinterpret the displayed situation (situation-focused volitional reappraisal) or to attend the picture without manipulating the emotional response to it (control condition). After each picture, participants were asked to rate their emotional state using a Self-Assessment Manikin for valence (SAM) [67], which served as the outcome measure. Pictures are selected from the International Affective Picture System (IAPS) based on normative ratings in valence and arousal [68].

For all functional scans T2*-weighted echo planar images (EPIs), sensitive to blood oxygenation level-dependent (BOLD) contrast will be obtained, covering the entire brain. Stress system dynamics in response to the TSST will also be assessed on the level of endocrine responses (salivary cortisol and alpha-amylase), psychophysiology (heart rate) and behaviour (in fMRI tasks). All task stimuli are presented using the stimulus presenter software Presentation (Neurobehavioral Systems, Albany, CA). Scanning protocols are identical for baseline and post-intervention assessments and are conducted at a 3 Tesla scanner at the Spinoza Centre for neuroimaging, Amsterdam, the Netherlands.

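### The fMRI sub-study plans to include exactly the 40 per arm that its power calculation needs as analysed, so the stated 80% power leaves no room for loss before T2

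*Protocol article*

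**What the plan says.** All the figures are in the Sample size section of the protocol article.

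- **Main trial.** The calculation ends with "This requires 63 participants per group". Earlier seven-day mifepristone trials in psychotic depression "found average dropout rates of around 20" percent, and the total is therefore raised to 158, or 79 per arm.
- **Sub-study, number needed.** The calculation concludes that "we need two equal groups of 40 individuals to detect a medium effect (Cohen's f = 0.32"). The test is a within-between interaction in a repeated-measures ANOVA with "2 groups (i.e. placebo and mifepristone) and 2 measures (i.e. acute and delayed phase"), intended to "obtain a power of 80 percent with type I error rate of 0.05".
- **Sub-study, number included.** The same paragraph opens with "40 participants will be included per treatment arm", a total of 80. It mentions no allowance for loss.

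The Neuro-imaging section says that the sub-study is conducted "at baseline (T0) and repeated at post-intervention (T2"), with an acute and a recovery session at each visit. Under Randomization and blinding, allocation is 1:1 and stratified by fMRI participation.

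**The concern.** Two adjacent paragraphs treat the same step differently. The main trial distinguishes the number needed for analysis (63) from the number to be recruited (79). The sub-study makes no such distinction: the number needed and the number included are both 40 per arm.

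The sub-study patients are a subset of the same randomised patients. The drug can affect only scans made after treatment, so a patient without a T2 scan adds nothing to the treatment comparison. T2 is also the time point of the main trial's primary outcome, so the dropout allowance made there concerns the same visit.

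What is at stake is how the result on the sub-study's primary imaging outcome is read. A null result would be presented as coming from a test with 80% power for a medium effect, when the patients actually scanned at T2 may support noticeably less.

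**Working it through.** **Inputs, all from the Sample size section:** f = 0.32; two groups and two measures; α = 0.05; target power 80%; 40 per arm needed and 40 per arm included; dropout of about 20%, stated for the main trial only.

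**Formula.** For a group-by-phase interaction with two groups and two measures, the test is an F test with 1 and N − 2 degrees of freedom and noncentrality λ = f² × N. Power is the probability that this noncentral F exceeds the 5% critical value.

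**Step 1: reproduce the plan's figures.**
- Sub-study: λ = 0.32² × 80 = 0.1024 × 80 = 8.19; critical F(1, 78) = 3.96; power = 80.7%. Solving for 80% power gives N = 78.6, which is 80 with equal groups. The stated 40 per group is reproduced.
- Main trial: 63 per group gives 126; 126 / 0.8 = 157.5, rounded up to 158. This also reproduces.

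**Step 2: how much slack there is.** At N = 79 power is 80.2%, and at N = 78 it is 79.7%. The loss of two patients is enough to fall below 80%.

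**Step 3: power under loss before T2 (f = 0.32, unadjusted group-by-phase test at T2).**

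| Loss | Completers | λ = 0.1024 × N | Power |
|---|---|---|---|
| 0% | 80 | 8.19 | 80.7% |
| 5% | 76 | 7.78 | 78.6% |
| 10% | 72 | 7.37 | 76.4% |
| 15% | 68 | 6.96 | 73.9% |
| 20% | 64 | 6.55 | 71.2% |
| 25% | 60 | 6.14 | 68.4% |

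**Step 4: detectable effect at 80% power.** With 80 completers, f = 0.317. With 64 completers, f = 0.356.

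**Step 5: number that would keep 80 completers at 20% loss.** 80 / 0.8 = 100, or 50 per arm.

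**Step 6: what the T0 scans could recover.** Take the acute-minus-recovery contrast at T2 as the outcome and the same contrast at T0 as a covariate. If r is the correlation between the two, residual variance falls by the factor 1 − r², so λ becomes f² × N / (1 − r²). The article gives no value for r, so these values are assumptions. With 64 completers:

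| Assumed r | λ = 6.55 / (1 − r²) | Power |
|---|---|---|
| 0 | 6.55 | 71.2% |
| 0.3 | 7.20 | 75.2% |
| 0.4 | 7.80 | 78.5% |
| 0.5 | 8.74 | 82.9% |

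These figures use N − 2 degrees of freedom. Taking off one more for the covariate (61 instead of 62) lowers them by less than 0.1 percentage point.

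**The case against.** **There is no miscalculation.** This stands. The stated inputs give the stated number. What is missing is an allowance for loss, in a section that makes one for the main trial.

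**The 20% is not a scanning dropout rate.** This also stands. It comes from seven-day trials in psychotic depression, while the sub-study is optional, separately consented and paid per visit. Its loss could be lower, or higher. That makes 71.2% a conditional figure, but it does not restore the 80%: even 5% loss gives 78.6%.

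**Delivered power is about 70%.** A reader might infer this as a flat statement. The documents do not support it. It needs the full 20% loss and an unadjusted test, and a figure just under 70% also needs f = 0.315 in place of the planned 0.32. The 0.315 describes a phase difference in healthy people, not the planned interaction, and at that value power is already 79.5% with nobody lost.

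**The calculation ignores the T0 scans, so power must be lower still.** A reader might infer this too, because the calculation has two measures while each patient is scanned in two phases at two visits. It does not follow. A group-by-phase comparison at T2 is a valid randomised comparison and matches the stated calculation. The article never commits to an analysis of change from T0. If one were used, the variance of the contrast would be multiplied by 2(1 − r): power would be lower than at T2 alone for r below 0.5, equal at 0.5 and higher above it. How T0 enters the model is also the kind of detail an article may leave to the full protocol or analysis plan.

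**Baseline adjustment might already be intended.** The article does not exclude it, and with an r of about 0.44 or more it would restore 80% at 64 completers. The stated calculation, however, has no such term, so it cannot be credited with the gain.

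**Conclusion.** The point holds in a limited form. The sub-study's 80% power applies to 80 patients with usable T2 scans, yet 80 is also the number to be included. Under the dropout assumption the article makes for its main trial, 64 would complete and power would be 71.2%, with a detectable f of about 0.36 instead of 0.32. Over 5% to 25% loss, power runs from 78.6% to 68.4%.

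These figures assume f = 0.32, the noncentrality convention that reproduces the article's own number, an unadjusted T2 test, and a loss rate borrowed from the main trial. They do not show that scanning at both T0 and T2 reduces power.

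The consequence is confined to the mechanistic sub-study. The 158 patients of the main trial and its IDS-SR analysis are untouched.

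**What to change.** 1. **Restate the power as conditional on completers.** For example: 80 included; 80.7% power if all are scanned at T2; about 71% with 64 completers, where the effect detectable with 80% power is about f = 0.36. Say that the 20% is carried over from the main trial. This costs wording only, and the stated power becomes less favourable.
2. **Use the T0 scans to recover precision.** Name as the primary fMRI test the group difference in the T2 acute-minus-recovery contrast, adjusted for the same contrast at T0 (ANCOVA). With 64 completers this gives about 75% to 83% power for assumed correlations of 0.3 to 0.5. It needs no extra scans and costs one degree of freedom. It should be fixed before the treatment codes are released.

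If 80 completers are wanted regardless of adjustment, the alternative is to include 100 (50 per arm) at 20% loss. That means 20 more patients scanned, so it is the costlier route.
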